##### Aids for abstinence

Intake and period of usage of different kinds of stop-smoking aids as supporting agents for tobacco abstinence will be investigated following therapy, after the 6-month and 12-month follow-ups. Assessments include medications authorized in Germany, such as nicotine patches, gums, sprays, sublingual tablets or other inhalants as well as bupropion (Zyban) and vareniclin (Champix). Additionally, the use of e-cigarettes will be evaluated. Results from a recent study suggest that e-cigarettes could significantly help in quitting the smoking of tobacco. In contrast, caution is advised because the long-term use of e-cigarettes indicates an addiction shift rather than actual abstinence from smoking [59]. Due to a lack of information on long-term health risks and new reports on vaping-induced lung injury, e-cigarettes are not primarily advised as a stop-smoking aid [66]. Use of e-cigarettes is critically discussed as a means of harm reduction, based on preliminary evidence available for either of the therapies [67]. We will assess the use of e-cigarettes and conduct analyses of this subgroup of participants in comparison to those using other stop-smoking aids.

##### Course evaluation

As measures for acceptance of the therapy, numbers of outpatient sessions attended will be assessed by the participants and by the therapists, separately. Reasons for discontinuation of therapy will be recorded. Satisfaction with the intervention will be evaluated on a 5-point Likert scale ranging from ‘not at all satisfied’ to ‘fully satisfied’. Therapeutic success will be evaluated on a 5-point Likert scale from ‘very low therapeutic success or condition worsened’ to ‘very good therapeutic success or condition much improved’. Furthermore, participants will be asked whether they would recommend the therapy with a dichotomous answer format (‘yes/no’).

##### The self-efficacy expectation for tobacco abstinence

Confidence to cope with typical high-risk situations for smoking will be assessed with the ‘Selbstwirksamkeits-Skala zur Rauchentwöhnung’ (SER [51]), the German short form of the Smoking Abstinence Self-Efficacy Scale [68]. The scale consists of nine items that are rated on a 5-point Likert scale ranging from 1 (‘not at all confident’) to 5 (‘very confident’) to generate an overall sum. A higher total score indicates higher self-efficacy expectation. The SER showed excellent internal consistency (α = 0.95) and a high retest reliability (*r* = 0.85 [51]).

##### Quality of life

Health-related quality of life will be assessed with the five-level German version of the EQ-5D (EQ-5D-5L [55]). This is one of the most commonly used instruments in general health assessment, available in more than 130 languages, and can be used for clinical and economical health evaluation [69]. The EQ-5D-5L consists of a descriptive system containing five dimensions (mobility, self-care, usual activities, pain/discomfort and anxiety/depression) and a visual analog scale to indicate the respondents’ overall state of health from ‘the best health you can imagine’ to ‘the worst health you can imagine’. The descriptive system is rated on a 5-point scale ranging from no problems to slight, moderate, severe and extreme problems [55]. The psychometric properties of the EQ-5D-5L have not been evaluated in a smoking sample to this date. However, the EQ-5D-5L has shown it can discriminate between smokers and non-smokers and can detect changes in quality of life after smoking cessation [70, 71].

##### Cost-effectiveness analysis

To evaluate efficacy from an economic perspective, therapy costs and subjective health gains will be compared between both groups. Indices for perceived health improvement on an individual level will be quality-adjusted life years (QALYs) calculated with the EQ-5D-5L [72, 73] at baseline and at the 12-month follow-up. Direct costs for the outpatient therapy and the residential therapy will be assessed; travel expenses will be estimated from the distance to the intervention locations and the type of transport. Incremental cost-effectiveness ratios (ICERs) are defined as costs per QALY gained [74]. Germany does not use a general willingness to pay threshold for cost-effectiveness (cf. the USA with $50,000 per QALY [75]). Therefore, willingness to pay for the therapy will be assessed directly from the participant’s perspective.

##### Motivation and volition

Very little is known about the processes that mediate successful smoking cessation [76–78]. Yet evidence points to the relevance of motivational and volitional processes [77]. To gain a deeper understanding of the intrapersonal processes necessary to gain and maintain abstinence from smoking, different stages of intention formulation and intention implementation will be assessed, based on the HAPA model [48]. To our knowledge, no standardized questionnaire for the assessment of the HAPA in smoking behavior has so far been published. Thus, items were adapted and translated from other HAPA studies on smoking behavior [48, 52, 53] as well as the recommendations of Sniehotta et al. [79] for measuring lifestyle change. Twelve items were generated to assess the processes of risk perception, smoking-specific self-efficacy expectation, outcome expectancies, intention to stop smoking, action planning, coping planning and action control to stop smoking. One item was designed to measure risk perception under social perspective: ‘Compared to people your age and gender, how would you estimate the likelihood that you will develop severe health problems (e.g. pulmonary diseases, cardiovascular diseases or cancer)’. This is rated on a 4-point Likert scale, ranging from 0 (‘much lower’) to 3 (‘much higher’) (see [48]). The other 11 items have been formulated as individual statements (e.g. ‘If I quit smoking, my health will improve.’) and rated on a 4-point Likert scale ranging from 0 (completely disagree) to 3 (fully agree). Items will be assessed at baseline and at the post-therapy and 12-month follow-up.

##### Adverse effects

Depressive mood and adverse events are assessed in order to record potential negative treatment effects and reasons for relapse. Residential smoking cessation programs have been shown to be safe in various contexts. Although no particular adverse effects of smoking cessation provided in a residential setting have been reported [40, 42], nicotine withdrawal symptoms [57] and adverse effects of therapy will be carefully protocolled, such as deterioration of mood and sleep.

Self-reported depressive symptoms will be collected with the PHQ-9 [54], the 9-item depression module from the Patient Health Questionnaire [80], at baseline, post-therapy and 12-month follow-up. The PHQ-9 assesses the frequency of adverse symptoms within the last 2 weeks on a scale from 0 (‘not at all’) to 3 (‘nearly every day’). The sum score ranges from 0 to 27, with cutoff points of 5 for mild, 10 for moderate, 15 for moderately severe and 20 for severe depression [81, 82]. Indications of suicidal ideation are covered in the last item of the questionnaire (values > 0) and will be monitored at each point of assessment. Participants who affirm having had suicidal thoughts or thoughts of self-harm will be examined over the telephone by trained psychologists for risk assessment. Interviews will be protocolled. Despite its brevity, the PHQ-9 has a high reliability (strong internal consistency between α = 0.79 and 0.89 [80, 81]) and a high validity (comparable sensitivity and specificity to other depression questionnaires [82]).

According to currently available scientific literature, further adverse events such as irritability, aggressiveness, dysphoric mood, insomnia and increased appetite or weight gain will be monitored as well as side effects of the stop-smoking medication, such as vomiting, nausea and skin irritation of the nicotine patch (cf. [57, 58]). Lastly, reasons and dates of relapses will be assessed to identify high-risk situations which might not have been covered in one of the therapy groups. Likewise, number of days smoking as well as number and duration of attempts to regain abstinence will be evaluated.

### Participant timeline {13}

Please see Fig. 2 for the assessment overview.

### Sample size {14}

The sample size calculation is based on nicotine abstinence after 6 months as the primary endpoint of the trial. According to Hays et al. [21, 38] and clinical experiences in cooperation with our local network for smoking cessation, 6-month abstinence rates of ≈ 27% from outpatient smoking cessation under routine conditions are expected. At a two-sided significance level of α = 5%, the null hypothesis of equality of abstinence probabilities in both groups should be rejected with a power of 90%, if the residential program increases the abstinence probability to 50%. To date, no data on dropout rates for prospective controlled studies on residential smoking cessation are available. Therefore, estimations of dropout rates are based on published studies on outpatient behavioral therapy smoking cessation groups. At a conservative estimate, therapy-uptake dropout after randomization will be 40% (cf. [83], 31% (*n* = 139) [84]; 34% (*n* = 406)). Additionally, studies suggest a loss to follow-up rate after starting the therapy of 20% ([85], 5% (*n* = 558) [86]; 6% (*n* = 1041) [87]; 14% (*n* = 2707) [88]; 19% (*n* = 220)). Thus, we expect a total dropout rate of 52%. The primary analysis will be conducted according to the intention-to-treat principle including participants who started the smoking cessation program. For this analysis, participants whose smoking status cannot be assessed will be classified as non-abstinent. Under these assumptions, observed abstinence rates are expected to be 22% versus 40%, respectively. Based on a two-sided χ^2^ test, a sample size of 137 participants per therapy group is necessary. Accounting for the assumed therapy-uptake dropout, a total of 458 participants (229 per group) will be randomized.

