#### Implementation {16c}

The allocation sequence was generated by a statistician of the Clinical Trials Unit not involved in study planning or conduct. After receiving the randomization results from the Clinical Trials Unit, the investigators inform the participants about their group assignment by telephone and provide information regarding admission into their respective therapy groups.

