### Statistical methods

#### Statistical methods for primary and secondary outcomes {20a}

A logistic regression model will be used to assess the efficacy of the therapy on the primary endpoint of abstinence after 6 months. The therapy effect will be tested using the Wald test at a two-sided significance level of 5%, and as an estimate of the effect size, the odds ratios will be given with 95% confidence interval. If the hypothesis of no therapy effect on abstinence after 6 months could be rejected, based on the closed test procedure, a confirmatory test of the therapy effect on abstinence after 12 months will be performed at a two-sided significance level of 5% using the same analysis. Additionally, the following sensitivity analyses will be performed. These will be per-protocol analyses including only participants who have completed the entire therapy and provided data on their smoking status. Furthermore, missing data on smoking status will be handled using multiple imputation methods [94]. Due to possible non-random therapy-uptake dropout in both randomized groups, possible group differences will be accounted for in additional sensitivity analyses including all randomized participants regardless of therapy uptake. In this analysis, non-starters will be categorized as smokers. Based on the assumed abstinence probabilities and assumed minimum therapy-uptake rates, this analysis would lead to observed 6-month abstinence rates of 13% versus 24%. With 229 randomized participants per group, this leads to a power of 85%. Secondary analyses will be conducted to assess non-compliance. Comparisons involve participant baseline characteristics of dropouts (non-starters and dropouts after the start of therapy) and compliers.

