This study will have some limitations. First, the required time and effort for participation (e.g. leave from work, distance and travel time to the therapies) might differ between participants and the therapeutic groups, which could affect motivation and lead to a selective therapy-uptake dropout. To minimize this potential bias, advantages and disadvantages of both therapies will be outlined equally and discussed during screening. Participants are only included in the study if they are able and willing to participate in both the residential therapy and the outpatient therapy. Second, the extent and procedures of the outpatient smoking cessation programs might differ due to a large number of different external therapists conducting the intervention. To ensure a high comparability between therapies, the search for outpatient therapies is based on the BZgA register to ensure therapeutic qualification and all therapeutic rationales and procedures are screened for eligibility based on prospectively defined criteria. The residential smoking cessation therapy is designed to match the amount and content of the outpatient therapy. Therapists are committed to a strict therapeutic rationale to ensure comparable conditions in both groups. To account for potential differences in the extent of additional supportive interventions in both groups, comparative cost-efficacy analyses will be computed. As another limitation, we have different types of stop-smoking medication including e-cigarettes. Due to the sample size we can only assess these moderators in an explorative approach. Finally, the study sample will be too small to test for potential interactive effects between subject characteristics and therapy success. Thus, findings on subgroups of participants who are especially likely to profit from this type of therapy or subgroups especially likely to experience negative effects will remain preliminary.

On the other hand, this study will be the first randomized controlled study to examine residential therapy in conditions that are close to routine care, compared to outpatient smoking cessation already implemented. Results are expected to yield high internal validity while allowing for conclusions about this new therapy model which can be generalized for other contexts to influence and improve future smoking cessation therapies.

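### The confirmatory analysis is called intention-to-treat but leaves out randomised participants who do not start therapy, and the planned all-randomised analysis, which counts every non-starter as a smoker, cannot simply replace it

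*Protocol article*

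**What the plan says.** Sample size {14} defines the confirmatory population: "The primary analysis will be conducted according to the intention-to-treat principle including participants who started the smoking cessation program". It assumes 40% of those randomised will not start, then 20% loss to follow-up among starters, with unknown status counted as smoking. The Primary endpoint section under Measures also uses the intention-to-treat label but mentions only loss to follow-up, so the exclusion cannot be seen there.

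Statistical methods {20a} places the comparison of everyone randomised among the sensitivity analyses, "including all randomized participants regardless of therapy uptake. In this analysis, non-starters will be categorized as smokers", and gives it 85% power with 229 per group. The reason offered is that non-uptake may be non-random. The 12-month test follows the 6-month test in a closed procedure using the same analysis.

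On the order of events, Implementation {16c} says that after randomisation "the investigators inform the participants about their group assignment by telephone". Section {17b} calls the design unblinded. The Discussion says that time, leave and travel may differ between the groups, "which could affect motivation and lead to a selective therapy-uptake dropout". As mitigation it includes only people able and willing to attend either therapy. Trial status reports 155 randomised and 106 started.

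**The concern.** Intention-to-treat means analysing people as randomised. A set defined by starting therapy is formed after randomisation by people who know whether they face a nine-day stay at one clinic or weekly sessions near home. If the kind of person who starts differs between arms, the two groups of starters differ in their chance of quitting before any therapy is given. Equal overall uptake would not rule this out.

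At stake is the superiority claim itself. Both confirmatory tests use this population, section {20b} gives confirmatory weight only to the primary endpoints, and no rule says what follows if the all-randomised analysis disagrees. At the planned uptake, 0.40 × 458 ≈ 183 randomised participants would not count in the confirmatory test.

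**Working it through.** **1. The plan's own figures reproduce.** Inputs from {14}: 27% versus 50%, 20% loss, 40% non-uptake, two-sided 5%, 90% power.

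- Rates among starters: 0.27 × 0.8 = 0.216 (stated as 22%) and 0.50 × 0.8 = 0.40.
- n = [1.960·√(2·0.31·0.69) + 1.282·√(0.22·0.78 + 0.40·0.60)]² / 0.18² = (1.282 + 0.822)² / 0.0324 ≈ 136.6, so 137 per group.
- Randomised: 137 / 0.6 = 228.3, so 229 per group, 458 in all.
- All randomised, non-starters counted as smokers: 0.216 × 0.6 = 13% and 0.40 × 0.6 = 24%. Power with 229 per group is 86.0% (chi-square) or 84.9% (Wald test on the log odds ratio), matching the stated 85%.

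The sample-size arithmetic is sound. The fault lies in the population and its label.

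**2. Size of the selection effect when therapy makes no difference.** Assumed inputs, not in the documents: half the sample quits with probability 40% and half with 14% (mean 27%) whichever arm they are in and whether or not they start; 20% of starters and of non-starters are lost and counted as smoking; outpatient uptake is 60% in both halves; 229 are randomised per arm. Residential uptake in the two halves (likelier quitters first) is 70%/50% or 80%/40%, so overall uptake is 60% in both arms.

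Expected rates, with u₁ and u₂ the uptake in the two halves:
- Starters only: 0.8(0.40u₁ + 0.14u₂)/(u₁ + u₂)
- Everyone, non-starters counted as smokers: 0.8(0.40u₁ + 0.14u₂)/2
- Everyone, observed status: 0.8 × 0.27 = 21.6% in both arms

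Two-sided rejection rates of the unadjusted Wald test come from 200,000 simulated trials per scenario.

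| Analysis | Residential 70%/50% | Rejects | Residential 80%/40% | Rejects |
|---|---|---|---|---|
| Starters only | 23.3% vs 21.6% | 6.2% | 25.1% vs 21.6% | 10.1% |
| Everyone, non-starters = smokers | 14.0% vs 13.0% | 6.0% | 15.0% vs 13.0% | 9.4% |
| Everyone, observed status | 21.6% vs 21.6% | about 5% | 21.6% vs 21.6% | about 5% |

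The second row does not help much because overwriting keeps only the successes of starters, so selective starting still drives the contrast. That analysis compares the combined event of starting and being abstinent, not abstinence.

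**3. Power when observed status is used.** With uptake u and an assumed quit rate q among non-starters in both arms (20% lost, counted as smoking), the expected rates are 0.40u + 0.8q(1 − u) and 0.216u + 0.8q(1 − u). For u = 0.6 and q = 0.27 this is 0.240 + 0.086 = 32.6% versus 0.130 + 0.086 = 21.6%. The difference stays at 11 points while the variance grows. With 229 per group:

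| q | Power at 60% uptake | Power at 68% uptake (106/155) |
|---|---|---|
| 5% | 84% | 90% |
| 10% | 82% | 89% |
| 15% | 80% | 88% |
| 27% | 76% | 85% |

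The documents give no value for q.

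**The case against.** The protocol is open about the population, prespecifies the all-randomised analysis with its power, and plans a baseline comparison of dropouts and compliers. Selection is also countered in the design: willingness to attend either arm is required, both therapies are discussed evenly at screening, randomisation is close to the therapy dates, and the participant's cost is about €50 in both arms. The 40% is a conservative planning figure beside cited values of 31% and 34%; so far 49 of 155 (32%) had not started, and some of these may have been waiting. The scenarios above use assumed inputs, and their shifts of 1.7 to 3.5 points are small beside the 18-point design difference.

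Much of this stands. It lowers the likely size of the bias, but screening acts before allocation is known, and the protocol still plans for heavy non-uptake that it suspects of being non-random.

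A reader might go further than the documents allow in two ways. The first is to infer that the trial is biased towards residential therapy. Nothing establishes a direction: equally selective uptake in both arms (70%/50%) gives a rejection rate of about 4.9%, and selective uptake in the outpatient arm alone would work against residential therapy. The second is to treat the planned all-randomised analysis as the unbiased answer, available for a fall in power from 90% to 85%. Its overwriting rule carries nearly the same inflation, and the 85% belongs to that rule.

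**Conclusion.** The intention-to-treat label in {14} is wrong as written, and the confirmatory comparison at both time points is not protected by randomisation. That conclusion follows from the text and needs no assumption.

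The size does depend on assumptions. With the quit strata and uptake patterns above, the two-sided false-positive rate rises from 5% to about 6.2% or 10.1% for starters only, and to about 6.0% or 9.4% if all non-starters are counted as smokers. It returns to about 5% with observed status. The actual effect could be smaller, larger or in the other direction. Whether non-starters are already followed cannot be judged, because the flow chart and assessment schedule are not shown.

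**What to change.** In {14} and {20a}, make the comparison of all randomised participants, as allocated, the confirmatory analysis at 6 and 12 months. Use the observed smoking status of non-starters wherever it can be obtained, and class as smoking only those whose status is unknown. Keep the starters-only analysis as a sensitivity analysis under a name such as modified intention-to-treat, and align the Primary endpoint text. Do not promote the rule that all non-starters are smokers. If few non-starters are reached, the new analysis drifts back towards that rule, so report follow-up of non-starters by arm.

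Restate the power as a range over uptake and the non-starter quit rate (the table above), noting that 85–86% at 60% uptake requires that no non-starter quits. Even on that favourable assumption, keeping 90% at 60% uptake would need about 258 to 260 per group (516 to 520 in all, against 458).

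The cost is lower stated power and, if non-starters are not already followed, contact with roughly 0.316 × 458 ≈ 145 to 0.40 × 458 ≈ 183 people at two time points, or about 290 to 366 contacts through the existing online and telephone assessments. Cotinine kits for non-starters who report abstinence at 12 months come on top. No extra enrolment is needed unless 90% power must be kept.

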### Recruitment {15}

Participants are recruited throughout Germany with a diverse approach via networking therapists for smoking cessation and general practitioners, advertisements in local newspapers and on social networks, announcements in scientific journals, press releases from the University Clinic Freiburg and the Comprehensive Cancer Center Freiburg website.

### Assignment of interventions: allocation

#### Sequence generation {16a}

Participants are randomized between therapy groups in a ratio of 1:1. Block randomization with randomly varying block size is performed based on computer-generated lists. Block sizes are documented separately from the study protocol in a document that is not accessible to investigators.

